**Figure 3 figure3:**
[figure not shown]
Flowchart of the multicenter non–randomized controlled trial.

### Patient Participants and Recruitment

Patients at the Department of Respiratory Diseases, the Department of Neurology, and the Department of Pain Management at OUH, as well as the Department of Cancer at UNN, are eligible for participation in the study if they are 18 years of age or older, home-based, and able to fill out Norwegian questionnaires (Table 3). Both newly diagnosed or newly referred patients, those with a diagnostic history, and those already in outpatient care are eligible for inclusion.

Eligible patients are identified through an outpatient consultation or through patient lists. All patients receive written and oral information about the project from a nurse or physician before giving their consent. The patients are not regarded as consenting participants until they have signed the consent form and filled out the baseline questionnaire. To reduce contamination in the intervention arm, patients must consent and fill out the baseline questionnaire before accessing the digital intervention.

The recruitment of patients to the qualitative interviews after the intervention is based on their consent to receive information regarding the interviews. Purposive sampling is applied to reach a heterogeneous sample with a balanced diversity in age, gender, and use of the intervention. Thus, in-depth knowledge can be obtained from both high and low users.

**Table 3 table3:** Eligibility criteria for patients.

Patient groups	Inclusion criteria	Exclusion criteria
Patients with cancer	Cancer Receiving active treatment	Life expectancy: less than 6 months Expected need for follow-up: less than 6 months
Patients with interstitial lung disease (ILD)	ILD	Very low degree of function with risk of cognitive influence
Patients with epilepsy	Epilepsy	Complex causes of epilepsy Severe comorbidity Other planned or ongoing assessment and treatment, including assessment of unexplained illness or testing of medication
Patients with long-term, complex pain	Drug testing, adjustment, and dose reduction Self-administering medication	Comorbidity that directly affects the drug adjustment Interference with other ongoing treatment Cognitive impairment Not living at home

### Health Care Personnel Participants

Health care workers in the hospital departments are eligible for the qualitative interviews if they are affiliated with the included departments and have had a role in this project. This group includes leaders and health care workers, such as nurses and physicians, with hands-on management of patient follow-up through the intervention.

### Randomization and Blinding

This is a non–randomized controlled trial without blinding. Both patients and health care workers are familiar with the treatment arm to which the participants belong during the study.

### Outcomes to be Measured

#### Overview

The study will consider the elements affected by both external factors in the health care services and internal factors held by the patient. Patients will self-report on the questionnaires (Tables 4 and 5). Clinical parameters and information on the use of resources will be collected from electronic medical records. The primary outcome is the health literacy questionnaire (HLQ) domain 9 “understanding health information well enough to know what to do” [51]. This domain encompasses health actions relevant for a digital service, such as basic reading and understanding of health information, following instructions from health care workers, and the ability to fill out forms correctly. The secondary outcomes are health literacy, eHealth literacy, HRQL, and acceptability of the digital intervention (Table 4).

**Table 4 table4:** Outcome measures for health literacy, health-related quality of life, digital health literacy, satisfaction, and COVID-19.

Measures, domains, and variables				Response options		Scale		Interpretation		Time point				
										T0		T1		T2
**Health literacy**														
	**Health literacy questionnaire (HLQ) (5 of 9 domains)**													
		Feeling understood and supported by health care providers (4 items) Having sufficient information to manage my own health (4 items) Actively managing my own health (5 items)	All items have the same response options: strongly disagree, disagree, agree, or strongly agree		1-4		A higher score indicates a higher level of health literacy		✓		✓		✓	
		Ability to actively engage with health care providers (5 items) Understanding health information well enough to know what to do (5 items)	All items have the same response options: cannot do or always difficult, usually difficult, sometimes difficult, usually easy, or always easy		1-5		A higher score indicates a higher level of health literacy		✓		✓		✓	
**eHealth literacy**														
	**eHealth literacy questionnaire (eHLQ; 7 of 7 domains)**													
		Using technology to process health information (5 items) Understanding health concepts and language (5 items) Ability to actively engage with digital services (5 items) Feel safe and in control (5 items) Motivated to engage with digital services (5 items) Access to digital services that work (6 items) Digital services that suit individual needs (4 items)	All items have the same response options: strongly disagree, disagree, agree, or strongly agree		1-4		A higher score indicates a higher level of eHealth literacy		✓		✓		✓	
**Health-related quality of life (HRQL)**														
	**RAND 12 (2 of 2 domains)**													
		Physical health composite (6 items)	All items have their individual scoring, and the physical composite score is based on the following 6 items: General health (excellent, very good, good, fair, or poor) Moderate activities, and Climb several flights of stairs, are scored on: limited a lot, limited a little, or not limited at all Accomplished less (physical), and 5. Limited in any kind of work, are scored on yes or no Pain interference (not at all, a little bit, moderately, quite a bit, or extremely)		0-100		A higher score reflects good physical health.		✓		✓		✓	
		Mental health composite-12 (6 items)	Accomplished less (emotional) (yes or no) The following items have the same scoring: (all of time, most of the time, a good bit of the time, some of the time, a little of the time, or none of the time) Did work less careful Calm and peaceful Energy Downhearted and blue Social limitations (time)		0-100		A higher score reflects good mental health.		✓		✓		✓	
**Service User Technology Acceptability Questionnaire (SUTAQ; intervention arm only)**														
	**SUTAQ (5 of 5 domains)**													
		Perceived benefit (9 items) Kit as a substitute (3 items) Satisfaction (3 items)	All items have the same response options: completely agree, moderately agree, mildly agree, mildly disagree, moderately disagree, or strongly disagree		1-6		A higher score reflects higher satisfaction.				✓		✓	
		Privacy and discomfort (4 items) Care personnel concerns (3 items)	All items have the same response options: completely agree, moderately agree, mildly agree, mildly disagree, moderately disagree, or strongly disagree		1-6		Reversed scale, thus higher score reflects a higher concern.				✓		✓	
**Satisfaction in general**														
	Satisfaction with the outpatient service in general (3 items)		All items have their individual scoring. Satisfaction with treatment (very satisfied, satisfied, neither satisfied nor dissatisfied, dissatisfied, or very dissatisfied) 2. Benefit from treatment (much better, somewhat better, stayed the same, somewhat worse, or much worse)		1-6		A higher score reflects higher satisfaction.		✓		✓		✓	
	Satisfaction with the outpatient service in general (3 items)		Safer with digital outpatient services (Yes; Feel free to elaborate/ No; Feel free to elaborate)		Y/N		Yes–safer		✓		✓		✓	

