## Methods

In the following, the development of the digital outpatient service intervention is presented before the details of the planned trial. The aim of the planned trial is to evaluate whether this intervention can have positive impacts on outcomes, including health literacy, health-related quality of life (HRQL), digital health literacy, satisfaction, and use of health service resources. Qualitative interviews will provide in-depth knowledge about the intervention from the perspectives of patients and health care workers. Furthermore, possible care pathways that ensure the quality of care and efficiency of remote monitoring in digital outpatient care will be investigated. The reporting of the intervention was guided by the Template for Intervention Description and Replication (TiDiER) [34], the protocol is reported according to the SPIRIT (Standard Protocol Items: Recommendations for Interventional Trials) [35], and the PROMs are reported according to the SPIRIT PRO extension [36].

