### Analysis

#### Statistical Analysis

The baseline and follow-up variables will be presented descriptively. Continuous variables will be analyzed using the mean and the SD for normally distributed data and the median and the range if the data are skewed. Categorical data will be presented as counts and percentages. The mean change will be estimated by subtracting the baseline score from the follow-up score, both at 3 months and 6 months. Differences in mean changes in short-term and long-term variables will be modeled using a one-way ANOVA. To adjust for possible confounders, logistic regression models will include age, gender, education, and hospital department. Missing data will be handled according to the syntax and protocol of the standardized instruments, such as HLQ, eHLQ, SUTAQ, and RAND-12. The missing data in terms of dropout has been accounted for in the power analysis.

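### Two of the three general satisfaction items in Table 4 do not suit the plan's change-from-baseline comparison between arms, and the two ordinal items carry a 1-6 range for five options

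*Protocol article*

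**What the plan says.** The Methods section of the protocol article gives the trial's aim as an effect on outcomes including "health literacy, health-related quality of life (HRQL), digital health literacy, satisfaction, and use of health service resources". Table 4 has two places where satisfaction is measured. One is the "Service User Technology Acceptability Questionnaire (SUTAQ; intervention arm only"), ticked at T1 and T2. The other is the block on general satisfaction, ticked at all three time points with no arm restriction. Its three items are:

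- "Satisfaction with treatment (very satisfied, satisfied, neither satisfied nor dissatisfied, dissatisfied, or very dissatisfied")
- "Benefit from treatment (much better, somewhat better, stayed the same, somewhat worse, or much worse")
- "Safer with digital outpatient services (Yes; Feel free to elaborate/ No; Feel free to elaborate")

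The first two are given a 1-6 scale on which higher means more satisfied; the third is Yes/No.

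Under Statistical Analysis, "The mean change will be estimated by subtracting the baseline score from the follow-up score, both at 3 months and 6 months", and differences in mean change are then modelled by one-way ANOVA. The Discussion repeats the change-from-baseline approach for the outcome measures as a group. Neither place makes an exception for these items, although Statistical Analysis also says that categorical variables are summarised by number and percentage. On who is enrolled: "Both newly diagnosed or newly referred patients, those with a diagnostic history, and those already in outpatient care are eligible for inclusion".

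**The concern.** SUTAQ has no control group, so any controlled statement about satisfaction has to come from the three general items. Two of them have a problem of meaning that the general analysis rule does not handle.

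The benefit item asks whether the patient is better or worse. The comparison with an earlier state is already in the question, and taking away an earlier answer to the same question does not yield a measure of benefit.

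The safer item asks about digital outpatient services. At follow-up, intervention patients can answer from having used the trial's service. Controls, and everyone at baseline, cannot.

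At stake is a misleading result on one stated aim. A continuing benefit could appear as no change, and a difference between experience and expectation could be read as an effect of the intervention.

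**Working it through.** **Benefit item.** Inputs: five options (Table 4), higher meaning better (Table 4), change = follow-up minus baseline (Statistical Analysis). The article gives no item coding, so I assume much worse = 1, somewhat worse = 2, stayed the same = 3, somewhat better = 4, much better = 5. I take T2 to be the 6-month visit. With change D = R(T2) − R(T0):

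- much better at T0 and at T2: D = 5 − 5 = 0
- stayed the same at T0 and at T2: D = 3 − 3 = 0
- much better at T0, somewhat better at T2: D = 4 − 5 = −1
- much worse at T0, stayed the same at T2: D = 3 − 1 = +2

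The first two patients report quite different benefit and get the same score. The third reports benefit at both visits and scores negative. The fourth reports no benefit at T2 and has the highest score of the four.

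The T0 answer also has no common meaning. Patients already in outpatient care can rate the treatment they have had there; a newly referred patient may have none to rate. If the arm means at T0 differ by d, then

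difference in mean change = difference in mean T2 rating − d.

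Allocation is not randomised, and each department completes control recruitment before intervention recruitment begins (Study Design), so the mix of new and established patients may differ between arms. Part of d could then reflect that mix, and the subtraction would carry it into the result. The article gives no figures from which to size d.

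**Safer item.** Study Design says that only the intervention arm receives the digital service and that controls follow departmental routine. Patient Participants and Recruitment says that the baseline questionnaire is completed before access. Use of the trial's own service at the time of answering is therefore:

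- control: T0 no, T1 no, T2 no
- intervention: T0 no, T1 yes, T2 yes

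That is 4 of 6 cells without use of the service. At T1 and T2 each between-arm contrast sets a cell with use against a cell without.

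**Range.** Number of listed options against stated range for the single-scale rows of Table 4:

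- HLQ, the three agreement-scale domains: 4 options, 1-4, match
- HLQ, the two difficulty-scale domains: 5 options, 1-5, match
- eHLQ: 4 options, 1-4, match
- SUTAQ: 6 options, 1-6, match
- fear of COVID-19: 5 options, 1-5, match
- satisfaction with treatment: 5 options, 1-6, mismatch
- benefit from treatment: 5 options, 1-6, mismatch

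The stated 1-6 cannot be obtained from five options scored in unit steps from 1; that gives 1-5. It equals the range of the SUTAQ rows directly above.

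**The case against.** The case on the other side has real weight, and several parts of it stand.

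- **The satisfaction-with-treatment item is sound.** It is an ordinary current-state rating, asked at every visit with no arm restriction, and it supports a change comparison. A reader might infer that the satisfaction aim cannot be answered at all. The document does not support that.
- **The change rule is generic.** It does not name these items. The safer item is Yes/No and may fall under the rule for categorical variables. That is fair, and it means a mean-change test of this item is not clearly planned. It does not remove the problem, because percentages set side by side by arm would still compare unlike answers.
- **Controls may know other digital services.** The item label is generic, video consultations are among the clinic contacts to be counted, and use of health apps is asked at each visit. So a reader should not infer that controls have no digital experience; only non-use of the trial's service is certain. The control answers then mix expectation with other experience, which still does not make them a comparator for experience of this intervention.
- **A 'No' could mean no different or less safe.** The free-text invitation partly deals with this.
- **The options run from best to worst while a higher score means more satisfied.** A reader might take this as reversed coding. It is not evidence of that: listing order is not coding, SUTAQ and RAND-12 do the same, and the direction is stated.
- **The range error does not prevent a change score.** Correct: differences between the five options are unaffected once the codes are fixed in unit steps.

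What is not answered is the benefit item. It is an ordinal item with a stated numerical scale, ticked at T0, and it falls under the change rule as written.

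**Conclusion.** The point holds for two of the three items. Followed as written, the plan gives an uninterpretable score for the benefit item. The safer item cannot carry a between-arm effect claim, whether analysed as change or shown as percentages. The 1-6 range is a separate table error with little consequence of its own.

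The severity is minor. Satisfaction is in the aim but not in the formal list: "The secondary outcomes are health literacy, eHealth literacy, HRQL, and acceptability of the digital intervention (Table 4"). The satisfaction-with-treatment item keeps a controlled comparison available, and the primary outcome (HLQ domain 9) and the listed secondary outcomes are not affected.

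The conclusion rests on two assumptions: that the general change rule applies to the benefit item, since no exception is stated, and that the labels in Table 4 reflect the questions asked. The worked scores also use the 1-5 coding given above; other unit-step codings in the same direction give the same differences.

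**What to change.** 1. Compare the benefit item between arms on the T1 and T2 ratings themselves, without subtracting T0. The comparison remains non-randomised and needs the planned adjustment for confounders.
2. Report the safer item as experience in the intervention arm at T1 and T2, as for SUTAQ. Show the T0 and control answers descriptively and separately, with no between-arm effect claim.
3. Name satisfaction with treatment as the controlled satisfaction outcome, and say where it stands relative to the listed secondary outcomes.
4. Correct the range of the two ordinal items to 1-5.

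The cost is wording in the outcome table and the analysis section; no new data are needed. The downside is that the safer item no longer yields a controlled comparison.

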**COVID-19**														
	Perceived safety related to the COVID-19 pandemic (2 items)		Previously infected (yes or no)		Y/N		Yes–previously infected		✓		✓		✓	
	Perceived safety related to the COVID-19 pandemic (2 items)		Fear of COVID-19 (never, seldom, sometimes, often, or almost always)		1-5		A higher score reflects more fear		✓		✓		✓	

**Table 5 table5:** Background variables and clinical outcomes.

Variables			Response options		Time point				
					T0		T1		T2
**Background variables**									
	Gender	Male, female, or unwilling to answer		✓					
	Marital status	Unmarried, married, cohabitant, widow or widower, divorced, separated, registered partner, divorced partner, or surviving partner		✓					
	Education	No education or preschool education, elementary school, high school without diploma, high school with diploma, bachelor’s degree or university or college lower level, master’s degree or university or college higher level, or PhD or researchers training		✓					
	Employment status	Full-time, part-time, home-employed, pursuing further education, unemployed, disabled, or retired		✓					
	Lifestyle habits (3 items)	(1) Smoking (yes or no), (2) snuff (yes or no), and (3) alcohol consumption (yes, no, and if yes, how often)		✓					
	Digital skills (3 items)	(1) Use of smartphone (yes or no), (2) use of tablet (yes or no), and (3) use of computer (yes or no)		✓					
	Use of mobile health apps	Yes or no–if yes, specify which apps		✓		✓		✓	
**Clinical variables (from the medical record)**									
	Primary diagnosis			✓					
	Time since diagnosis or start of condition	Duration of condition		✓					
	Medication	Current treatment and any changes		✓		✓		✓	
	Comorbidities	Number of comorbidities		✓					
**Use of health care resources (from the medical record)**									
	Contact with the outpatient clinic	Contact type (physical consultation, video consultation, telephone call, or other), planned or acute, and number of each						✓	
	Use of the digital service (dose of intervention)	Contact type (PROM^a^ response, task, chat, video, or other) and the number of each						✓	

^a^PROM: patient-reported outcome measure.

#### Health Literacy

The HLQ is a multidimensional measure of health literacy, with 44 questions across 9 domains. The HLQ is validated for adults using various modes of administration, including computer-based [51,52]. The HLQ was developed in Australia, translated into Norwegian, and used in studies on chronic diseases [51,52]. To reduce overlap with the domains of the eHealth literacy questionnaire (eHLQ), 5 of the HLQ domains (domain 1,2,3,6, and 9) that represent all 3 levels of the Nutbeam model have been included in this study [14]. Domains 2 and 9 are at the basic level; domains 1, 3, and 6 are at the communicative level, while domain 3 is at the critical level of health literacy [51].

#### eHealth Literacy

The eHLQ is multidimensional with the same origin as the HLQ, assessing people’s interactions with digital services based on the eHealth literacy framework [53]. The eHLQ contains 35 questions over 7 domains, and the full questionnaire is applied in this study. Although the eHLQ is translated into Norwegian and used in Norway, it is not yet validated. Validation in Denmark shows good psychometric properties [53].

#### HRQL

To assess HRQL, the patients fill out the RAND-12 [54,55], an abbreviated version of its predecessor, the SF-36. The 12 items are summarized into 1 physical and 1 mental health composite. The RAND-12 is validated in Norwegian [56].

#### Acceptability of the Digital Intervention

To assess acceptability among the participants assigned to the intervention arm, the patients fill out the service user technology acceptability questionnaire (SUTAQ). Acceptability refers to whether a system is good enough to satisfy users’ needs and requirements. The SUTAQ also assesses the importance of having contact with health care workers and whether this may affect patients’ acceptance [57,58]. The SUTAQ has 22 items across 5 domains. The participants are instructed to keep the digital outpatient service intervention in mind when responding. The SUTAQ has been translated into Norwegian, psychometrically tested [58], and is used in Norway for patients with type 1 and type 2 diabetes.

### Qualitative Evaluation Measures

Individual qualitative interviews will be conducted following the same structure for patients in the intervention group and the health care workers. The interviews will explore the interviewees’ perceived satisfaction with the digital outpatient service, and security in and beyond pandemic situations. The semistructured guide has been developed by the research team, inspired by topics on innovation assessment [59] and is added as a Multimedia Appendix 4. The aim of the qualitative interviews is to gain in-depth knowledge about the components of the intervention, how they are used, and whether and how they are perceived as useful. The interviews are also intended to obtain in-depth knowledge about how the digital intervention differs from traditional consultations and how these differences are perceived. In line with the primary outcome of health literacy obtained from the quantitative measures, any experiences of improved or otherwise affected health literacy will be investigated. Accordingly, the same guide will be applied to health care workers, tailored to their profession.

